## Abstract

**Background:**

Cognitive behavior therapy for psychosis (CBTp) is an effective intervention for people who hear distressing voices (auditory hallucinations). However, there continues to be a problem of poor access to CBTp. Constraints on health care funding require this problem to be addressed without a substantial increase in funding. One solution is to develop guided self-help forms of CBTp to improve access, and a symptom-specific focus on, for example, distressing voices (auditory verbal hallucinations) has the potential to enhance effectiveness. We term this *cognitive behavior therapy for distressing voices* (CBTv).

**Methods/design:**

This trial is an external pilot randomized controlled trial comparing the effects of 12-week guided self-help CBTv (with eight therapist support sessions) with a wait list control condition. Informed consent will be obtained from each participant. Half of the 30 participants will be randomized to receive guided self-help CBTv immediately; the remaining half will receive the intervention after a 12-week delay. All participants will continue with their usual treatment throughout the study. Outcomes will be assessed using questionnaires completed at baseline and 12 weeks postrandomization. Interviews will be offered to all those who receive therapy immediately to explore their experiences with the intervention.

**Discussion:**

The outcomes of this trial, both quantitative and qualitative, will inform the design of a definitive randomized controlled trial of guided self-help CBTv. If this intervention is effective, it could help to increase access to CBT for those who hear distressing voices.

**Trial registration:**

ISRCTN registration number ISRCTN77762753. Registered on 23 July 2015.

## Background

Hearing voices (i.e., auditory verbal hallucinations) is a common experience [1]; some people find this experience very distressing and hear voices in the context of a mental health problem [2]. Hearing distressing voices is a symptom of psychotic spectrum disorders, such as schizophrenia [3], but voices can also be present in the context of other mental health conditions, such as borderline personality disorder [4], dissociative identity disorder [5], bipolar disorder [6], and posttraumatic stress disorder [7].

The authors of a meta-analysis found cognitive behavioral therapy for psychosis (CBTp) to be an effective treatment for distressing voices [8]. National treatment guidelines issued in a number of countries recommend that everyone with a psychotic disorder be offered CBTp [9–11], with the guidelines stating that at least 16 individual sessions of CBTp should be offered.

Despite evidence for its effectiveness and recommendations in national treatment guidelines, CBTp is not widely available. Even though the United Kingdom has led the way in promoting the implementation of CBTp [12], the authors of a report by the U.K. Schizophrenia Commission [13] found only 10 % of people with psychosis were offered CBTp. More recent figures suggest this rate may have actually decreased [14].

The most consistently reported barrier to implementation is insufficient resources to meet the demand, including both insufficient numbers of therapists trained in providing CBTp [15] and trained therapists’ lack of protected time [14]. The current economic climate has had a deleterious impact on mental health funding across the globe [16]. Consequently, it is not realistic to expect that resources required to deliver CBTp in line with treatment guidelines will be available in the near future. An alternative approach is to use available resources more efficiently. This could include offering CBTp self-help resources with a therapist’s guidance, an approach that requires less therapist resources than standard interventions [17]. We propose a guided self-help form of CBTp that could be a suitable intervention for this client group. Our approach requires less therapeutic contact time (8 sessions) than the recommended 16 sessions, so the same number of therapists could, in principle, offer an intervention to twice as many people over the course of a year.

The authors of multiple meta-analyses have found that guided self-help cognitive behavioral therapy (CBT) is effective for treatment of anxiety and depression [18, 19], and, as a consequence, guided self-help CBT is offered routinely in the United Kingdom for people experiencing these difficulties [20]. Evidence is emerging that briefer forms of CBTp may also be effective. A meta-analysis found that, in comparison to control conditions, briefer forms of CBTp (i.e., trials offering fewer than the recommended 16 therapy sessions) significantly improved psychosis symptoms at posttherapy and during follow-up [21]. However, the authors of a previous meta-analysis of CBTp more broadly showed that trial quality is an important moderator of treatment effects; with high-quality CBTp trials producing smaller effect sizes than lower-quality trials [22, 23]. Therefore, lower-quality trials may overestimate the effectiveness of briefer forms of CBTp.

In addition, in an effort to improve the effectiveness of CBTp, the field is moving away from generic CBTp for the broad range of psychotic symptoms and toward symptom-specific CBTp, with recent trials being focused on CBTp for delusions [24] and distressing voices [25]. However, to our knowledge, there has been no research into the potential of guided self-help for distressing voices, and this is the aim of the present study.

This study is an external pilot randomized controlled trial (RCT) being conducted prior to a definitive trial of guided self-help CBTp for people distressed by hearing voices (which we term *CBTv*). Guided self-help CBTv aims to reduce the distress associated with the experience of hearing voices. Therefore, the primary hypothesis for the trial will be that, compared with the delayed therapy control group, those who receive guided self-help CBTv will experience a reduction in the distress associated with voices. Secondary hypotheses will be that those receiving guided self-help CBTv will report improvement in negative and positive beliefs about voices, self-esteem, and assertive relating in comparison with the control group, which are the mechanisms through which the therapy is proposed to work [26].

The following are the aims of the present pilot study: (1) to determine whether a full trial is justified, (2) to establish the effect size on the primary outcome (voice-related distress) for a sample size calculation for a definitive trial, and (3) to address questions concerning study recruitment, retention, and acceptability. Specifically, between-group treatment effects will determine whether a definitive RCT of guided self-help CBTv is justified; that is, we will proceed if the effect size on the primary outcome is in favor of CBTv in comparison to the delayed therapy control condition and if the 95 % CI for this effect contains the minimal clinically important difference (MCID). If so, this study will provide the parameters needed to estimate the sample size for a definitive RCT. Finally, we will assess whether the study design is acceptable to participants using recruitment and retention rates and qualitative interviews with participants. Both study dropout and therapy dropout rates will be reported with a view to understanding reasons for dropout and developing strategies to minimize dropout in a definitive trial.

## Methods/design

This study is a pragmatic, single-blind, external pilot RCT with two parallel arms and 1:1 allocation. A rater blinded to allocation will conduct postintervention assessments. A total of 30 participants will be recruited; half will be randomly allocated to receive guided self-help CBTv immediately (immediate therapy), and half will join a wait list for the same intervention (delayed therapy). Both groups will maintain their usual mental health care throughout the course of the study.

The randomization of participants will be conducted by an independent statistician, using a 1:1 ratio random permuted block randomization (with block sizes of two, four, and six). The research team will be blinded to the block size. Figure 1 illustrates the process of randomization and group allocation.

**Fig. 1 Fig1:**
[figure not shown]
Consolidated Standards of Reporting Trials (CONSORT) diagram of participant progression through the Guided self-help cognitive behavioral intervention for VoicEs trial. *CBTv* cognitive behavioral therapy for voices, *TAU* treatment as usual

The outcome data will be collected at time 0 (before randomization), and at time 1 (12 weeks postrandomization). Time 1 assessments will be conducted by a research assistant blinded to the participant’s group allocation. All of the participants allocated to receive immediate therapy will be asked to complete an exit interview to discuss their experience with the therapy.

To assess adherence to the protocol, all therapists will be asked to complete a checklist after each session with each client, indicating the elements of the protocol they have covered. The checklist has been designed specifically for this intervention.

### Participants

Participants will be service users recruited from an NHS mental health trust in the South of England. Clinicians will be asked to refer eligible service users from among their caseload. Potential participants will also be identified using a database of people who have agreed to be contacted about research studies.

In line with the recommendations of Julious [27] for pilot RCTs, 12 participants per arm are required for this pilot RCT. The authors of a meta-analysis of briefer forms of CBTp found the maximum dropout rate to be 13.5 % [21]. Using this as a guideline, we have overestimated a potential attrition rate of 20 % for the present study, meaning a total of 30 participants will be recruited (15 per arm).

The inclusion criteria for participants are that they must (1) be aged 18 years or older; (2) be distressed by hearing voices; which will be operationalized by requiring participants to score at least 3 out of 5 on item 5 (How much do the voices interfere with your daily activities?), 6 (How distressing are the voices that you hear?), or 7 (How bad do the voices make you feel about yourself) on the Hamilton Program for Schizophrenic Voices Questionnaire (HPSVQ) [28], equivalent to moderate levels of interference, distress, and impact, respectively; (3) have heard voices for the at least 1 year; (4) are not currently in, or have plans to receive, another psychological intervention during the course of the study; and (5) are able to read and write in English at the level required for the self-help course.

Participants will be excluded from the trial if they have a primary diagnosis of substance misuse or if an organic illness is determined as the reason for hearing voices. Otherwise, diagnosis is not an inclusion or exclusion criterion, given that distressing voices are common across a range of diagnoses (i.e., schizophrenia [3], borderline personality disorder [4], dissociative identity disorder [5], bipolar disorder [6], posttraumatic stress disorder [7]).

### Planned intervention

The 12-week intervention is based on and guided by the self-help book *Overcoming Distressing Voices* [26] and an accompanying workbook that summarizes the key chapters. The therapists and participants will have the same therapy materials (book and workbook). Therapist guidance will be offered over a maximum of 8 sessions (30–60 minutes per session) delivered over the 12 weeks. The intervention will be guided by clinical psychologists with expertise in CBTp, and participants will be encouraged to engage with the structured self-help workbook throughout. The intervention protocol has been developed in collaboration with clinicians and people with lived experience of hearing voices.

The intervention consists of five modules: (1) The Coping module will look at ways of managing voice distress; current coping strategies will be evaluated, and new ones considered; (2) the Me module will address self-esteem; negative beliefs about the self will be re-evaluated, and positive beliefs will be strengthened; (3) the My Voices module will target unhelpful beliefs that are typically associated with voices, focusing on re-evaluating these beliefs; (4) the My Relationships module will give the participant an opportunity to work on a difficult relationship (including the relationship with voices), the aim being to develop more assertive ways of relating; and (5) the Looking to the Future module offers an opportunity for reflection and develops a plan for taking learning from the self-help course forward into the future.

Participants will keep the book and workbook after therapy has ended, providing a resource they can return to at a later date. Participants will be free to drop out of the intervention at any point. Therapists will each receive training in the intervention from CS and MH (authors of the self-help book), and monthly therapist group supervision will be offered.

### Wait-list control (delayed therapy)

Participants allocated to delayed therapy will join a waiting list for the intervention. The waiting period will be approximately 12 weeks after randomization, at which point participants will receive the intervention as outlined above.

Throughout the trial (including the waiting period), participants will continue with their usual mental health care. This will likely involve taking psychiatric medication and having regular contact with a clinician. The type of medication participants are taking, as well as any changes in these across the span of the study, will be recorded.

### Measures

The primary outcome will be the HPSVQ voice impact subscale [28]. The HPSVQ voice impact subscale has five items rated on a 5-point (0–4) scale and measures the level of distress and impact that voices have on the person. The phenomenology subscale (four items) will also be included in this trial (and will be a secondary measure in the definitive trial). The questionnaire contains nine items in total and has strong concurrent validity (all *r* > 0.80) as well as good internal consistency (all α > 0.82) [29].

The following measures of secondary outcomes are also included in this trial:The Choice of Outcome in CBT for Psychoses questionnaire [30] was developed in partnership with service users. It has 22 items measuring service user-defined recovery. Two of the items give participants the opportunity to include their own recovery goals for CBT. The severity scale of this questionnaire has a high level of test-retest reliability (α = 0.83).The Hospital Anxiety and Depression Scale (HADS) [31] measures clinical levels of anxiety and/or depression. The HADS has 12 items. The English version of this questionnaire has good internal consistency (α = 0.80) [32].The Short Warwick-Edinburgh Mental Well-being Scale (SWEMBS) [33] uses seven items to measure psychological well-being. The SWEMBS has demonstrated good reliability (α = 0.91).The Rosenberg Self-Esteem Scale (RSES) [34] consists of ten items. It was originally developed to measure self-esteem among adolescents, but it has since been used with adults with strong psychometric properties. The RSES has strong levels of test-retest reliability over time (*r* = 0.85).The Brief Core Schema Scale (BCSS) self-scale [35] measures participants’ endorsement of positive and negative beliefs about themselves. The BCSS self-scale has 12 items and has strong internal consistency when given to clinical participants (α = 0.84).The Person’s Relating to Others Questionnaire short version (PROQ3) [36] measures social relating (person to person) in terms of their proximity and power. The questionnaire includes 48 items, and all scales show acceptable levels of internal consistency (all scales α > 0.70).The Voice and You [37] measures the same relational dimensions as the PROQ3 [36] but in the context of the participant’s relationship with their voices (hearer to voice). The scale has 28 items and demonstrates good internal consistency across all of the scales (all scales α > 0.80).The Beliefs about Voices Questionnaire–Revised [38] has 35 items and measures the strength of a range of beliefs about voices. All scales have acceptable levels of internal consistency (all scales α > 0.74).

Sessional measures will be taken using six visual analogue scale questions, with each question targeting an intended therapy outcome or mechanism. An exit interview will be administered postintervention to participants in the immediate therapy condition. The Change Interview [39] will be used at that time to ask participants to consider any changes they have experienced over the course of the intervention and, if so, what they attribute these changes to. Helpful, unhelpful, and missing aspects of the intervention are also explored within the Change Interview. The Change Interview also asks participants to provide feedback on their experience with the research study itself, as well as to provide suggestions for future research in the area. The exit interview will also include additional questions on participants’ experiences of the study process (e.g., assessments, consent, randomization) [40].

### Data collection and storage

All data will be collected and stored in line with the Data Protection Act (1998). Assessments will be completed using tablet computers so that data are entered and stored electronically. Anonymized data will be stored on password-protected computers and will be available to members of the research team. Any files that contain personal information of participants will be kept in a password-protected electronic file or in locked filing cabinets on NHS or university sites. To maximize study retention, participants will be invited to complete postintervention assessments even if they have dropped out of the intervention, and all assessments will be conducted at a time and place most convenient to the participant.

### Planned analysis

All of the analyses will be carried out once data collection has been completed. IBM SPSS Statistics version 22 software (IBM, Armonk, NY, USA) will be used to conduct all quantitative analyses. The findings of this trial will be reported using the Consolidated Standards of Reporting Trials (CONSORT) guidelines. The recruitment rates for this trial will be reported as a ratio of the number of potential participants approached to the number who consent to participate. The retention rates will be reported first as the percentage of participants who drop out of the study (i.e., do not complete time 1 assessments) and second as the percentage of participants who drop out of therapy before exposure (receive fewer than four sessions). If study or therapy dropout rates are greater than 33 %, this will indicate that changes to the study and/or therapy protocols may be needed. The acceptability of the study and therapy will be assessed using retention rates and feedback obtained through the exit interview.

The analysis for this trial will be mostly descriptive. We will report the means and/or medians (as appropriate) as well as SD and minimum and maximum scores at time 0 and time 1 for both groups on primary and secondary outcomes. Participants’ characteristics will be reported using frequency counts and percentages, including the characteristics of any participants who drop out of the study and/or therapy. Analysis of covariance will be used to estimate T1 between-group differences on primary and secondary measures, controlling for baseline scores. Ninety-five percent confidence intervals will be calculated. Effect sizes will be reported as Cohen’s *d* (unstandardized effect size divided by the baseline pooled SD). We will look at the effect sizes using both an intention-to-treat analysis approach and a per-protocol analysis (looking only at participants who attended at least 50 % of therapy sessions). A definitive trial will be considered to be justified if there is a between-group effect in favor of CBTv on the primary outcome (HPSVQ voice impact subscale [28]) and if the 95 % CI contains the MCID of 2 points in favor of CBTv.

The exit interviews will be transcribed into NVivo software files (QSR International, Doncaster, Australia) and analyzed using thematic analysis in accordance with the Braun and Clarke [41] protocol. The aim of the analysis will be to identify common patterns across interviews that reflect the participants’ experiences of therapy and of the study processes. These themes, as well as the quantitative results, will be used to refine the study and therapy protocols. If a definitive trial is justified, then the power calculations will be based upon the between-groups effect size on the HPSVQ voice impact subscale [28].

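### The pilot's effect size is Cohen's d with no small-sample correction, which at 12 to 15 per arm overstates the standardized effect by about 3% on average: a minor bias, free to remove

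*Protocol article*

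**What the plan says.** All references are to the protocol article.

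- **Estimator (Planned analysis).** "Analysis of covariance will be used to estimate T1 between-group differences on primary and secondary measures, controlling for baseline scores". The result is to be reported as Cohen's d, defined as the "unstandardized effect size divided by the baseline pooled SD". The formula is written out and has no small-sample factor. It serves the primary and secondary measures, under both intention-to-treat and per-protocol analysis.
- **Use (Planned analysis).** If a definitive trial is justified, "the power calculations will be based upon the between-groups effect size on the HPSVQ voice impact subscale". The aims at the end of the Background likewise list establishing this effect size for a sample size calculation.
- **Size (Participants).** "12 participants per arm are required for this pilot RCT". With an allowance for 20% attrition, 15 per arm are to be recruited.
- **Decision to proceed (Background and Planned analysis).** The estimate must favour the intervention, and its 95% confidence interval must contain a difference of 2 points on the HPSVQ voice impact subscale. This rule is on the raw scale.

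**The concern.** A ratio with a sample SD in the denominator is biased away from zero in small samples, because the mean of 1/S is larger than 1/σ. If the analysis-of-covariance model holds, the adjusted difference is unbiased whatever the baseline values are. The average of d is then the true difference times the mean of 1/S, and so exceeds the true standardized effect. Jensen's inequality fixes the direction without any need for normality; only the size depends on the distribution.

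Two things are at stake. The standardized effects in the pilot report would, on average, look slightly better than they are. If the definitive trial is sized from d, the same bias enters that calculation. The Background itself warns that weaker trials may overestimate briefer forms of this therapy, so a known upward bias is worth removing if that is free.

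**Working it through.** **1. The plan's own figure.** 12 / (1 − 0.20) = 15 per arm, 30 in total. This reproduces the stated sample size.

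**2. Degrees of freedom of the pooled SD.** The article does not say whose baseline scores enter the SD, so both cases are shown.
- Completers only, 12 per arm: 2 × 12 − 2 = 22.
- All randomized, 15 per arm: 2 × 15 − 2 = 28.

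**3. Average bias under normality.** The exact factor is J(df) = Γ(df/2) / [√(df/2) · Γ((df − 1)/2)], and d is too large on average by 1/J − 1.

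| df | J exact | 1 − 3/(4·df − 1) | 1/J − 1 |
|---|---|---|---|
| 22 | 0.9655 | 1 − 3/87 = 0.9655 | 3.6% |
| 28 | 0.9729 | 1 − 3/111 = 0.9730 | 2.8% |

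**4. Check on the planned estimator.** Simulating the adjusted difference over the baseline pooled SD, with normal scores and 100,000 pilots, gave +3.6% (12 per arm) and +2.8% (15 per arm). Shorter runs of 40,000 gave +2.5% to +4.6%, with a simulation error of about 0.4 points. With flat instead of normal baseline scores the bias was +1.4%.

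**5. Bias against sampling error.** Assume a true d of 0.5; the article gives none. The bias is 0.5 × 0.036 = 0.018 or 0.5 × 0.028 = 0.014. The simulated standard error of d was about 0.36 (12 per arm) or 0.32 (15 per arm) with an assumed baseline-to-12-week correlation of 0.6, and 0.39 or 0.34 with 0.5. The ratio is about one twentieth. About 49% of simulated d values fell below the truth.

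**6. Effect on a computed sample size.** The article gives no power, alpha or target effect for the definitive trial. Assume 80% power, two-sided 5% and a true d of 0.5: n = 2 × (1.96 + 0.84)² / 0.5², or 63 per arm.
- *Plug-in at the mean of d.* n is multiplied by J², which is 0.932 or 0.947, so it is 6.8% or 5.3% lower: 59 or 60 per arm, with real power of 77.5% or 78.2%.
- *Average over pilots, for a given difference.* n is proportional to S²/difference². S² is unbiased for the variance, so the SD causes no average shortfall. Its median effect is −3.0% (22 df) or −2.4% (28 df).
- *Difference and SD both varying.* Among simulated pilots with a favourable effect (correlation 0.5), the median computed n was 53 using d and 57 using g (12 per arm), or 56 and 60 (15 per arm), against the right 63.
- *Spread.* The middle 80% of computed sample sizes ran from about 0.25 to 8 times the right one.

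**The case against.** The strongest objections, and what stands of each:

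- **The sample size is not 5% to 7% too small.** A reader might infer this from the square of the correction factor. That figure is a plug-in value at the mean of d, not an average property of the computed n. The objection stands in full.
- **Using g may not improve the sample size.** For a given difference, g multiplies n by 1/J² (1.073 or 1.056), so n becomes about 7% or 6% too large on average instead of unbiased. In the median it is 4.0% or 3.1% too large (0.970/0.932 and 0.976/0.947), against 3.0% or 2.4% too small. This is right with the difference held fixed. In practice the difference varies too, and among favourable pilots g brings the median n nearer to 63. It also has the lower root mean squared error as an estimate of the effect: 0.376 against 0.389 (12 per arm) and 0.333 against 0.342 (15 per arm).
- **The power calculation may not use d.** The article speaks there of the between-groups effect size without naming Cohen's d, and uses the term effect size for the raw difference too. If the raw difference and an SD are used, the standardization bias does not arise. This stands, so the advice on power must be conditional.
- **It is a convention that a condensed article may leave to a fuller plan.** Uncorrected d is common, nothing is contradictory, and readers could convert d themselves. But the article states the formula, so this is a stated estimator and not an omitted detail. The objection limits the weight of the point without removing it.
- **The correction is not exact here.** It is exact only under normality. The voice impact subscale runs from 0 to 20 (five items scored 0 to 4), and entry requires a minimum score on one of three HPSVQ items. This stands.

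**Conclusion.** The point holds as a low-priority improvement. The stated estimator overstates the true standardized effect on average by about 3.6% (22 df) or 2.8% (28 df). This assumes that the analysis-of-covariance model is right and that scores are roughly normal; it does not depend on the assumed d of 0.5.

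A reader might also infer that every reported effect will be too large. The documents do not support that: the bias is an average, and close to half of individual estimates would fall below the truth. Nor can a multiplier on d change the decision to proceed, which rests on the direction of the effect and on raw points.

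The imprecision of a pilot effect size as a basis for power is far the larger problem, and correcting d does not address it.

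**What to change.** In Planned analysis, replace Cohen's d by Hedges' g: d multiplied by 1 − 3/(4·df − 1), where df are the degrees of freedom of the baseline pooled SD. State whether that SD uses all randomized participants or completers only. Report g with its 95% confidence interval for the primary and secondary outcomes, and recompute df for the per-protocol set if its SD comes from fewer participants. Note that the correction is approximate for a bounded subscale.

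Where the section refers to the definitive trial's power calculation, add that if a standardized effect is used, it will be g.

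The cost is one multiplication per outcome, with reported effects about 3% less favourable. Design, data collection and the decision rule stay as they are.

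### The progression rule asks the 95% CI to contain the 2-point MCID, so read literally a CI lying wholly above 2 points does not meet it

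*Protocol article*

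**What the plan says.** The rule appears twice in the protocol article.

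- **Planned analysis:** "A definitive trial will be considered to be justified if there is a between-group effect in favor of CBTv on the primary outcome", joined to a second condition that the 95% "CI contains the MCID of 2 points in favor of CBTv".
- **Background, aims paragraph:** "we will proceed if the effect size on the primary outcome is in favor of CBTv" over delayed therapy, and if the 95% "CI for this effect contains the minimal clinically important difference (MCID").

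The estimate behind the rule is the baseline-adjusted difference at 12 weeks: "Analysis of covariance will be used to estimate T1 between-group differences on primary and secondary measures, controlling for baseline scores". The next sentence adds "Ninety-five percent confidence intervals will be calculated". On the scale, Measures says "The HPSVQ voice impact subscale has five items rated on a 5-point (0–4) scale", so the total runs from 0 to 20.

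Neither statement of the rule adds that the interval may also lie above the MCID, and neither gives a different decision for that case. The last paragraph of Planned analysis makes the power calculation for the definitive trial conditional on that trial being justified.

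**The concern.** A progression rule for a pilot should be at least as easy to pass when the observed benefit is larger. A containment rule is not. It is failed by an interval wholly below 2 points, which is sensible, and also by an interval wholly above 2 points, which is the strongest result the pilot can give. The chance of meeting the literal rule therefore rises with the true benefit and then falls.

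Whether a full trial is justified is the first listed aim of the pilot. If the result were strongly favourable, the team would have to interpret its own pre-specified rule after seeing the data, which is what pre-specification is meant to avoid.

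**Working it through.** **1. The plan's own figure.** Participants states "12 participants per arm are required for this pilot RCT" and allows for 20% attrition: 12 / (1 - 0.20) = 15 per arm, 30 in total. This matches the protocol, so 12 analysed per arm is used below.

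**2. The rule as logic.** Let benefit be positive when it favours CBTv, with estimate E and 95% limits L and U. The literal rule is E > 0 and L ≤ 2 ≤ U.

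- CI 2.5 to 8.5: E = 5.5, L = 2.5 > 2, so the rule is not met.
- CI -1 to 5: E = 2, and L ≤ 2 ≤ U, so the rule is met.

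This step needs no assumption.

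**3. Can it happen at this sample size?** The protocol gives no SD for the subscale and no baseline-to-12-week correlation. Assumed: SD 3, 4 or 5 points; correlation ρ = 0.5; n = 12 per arm; residual df = 2n - 3 = 21.

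- SE = SD × √(1 - ρ²) × √(2/n). For SD 4: 4 × 0.866 × 0.408 = 1.41.
- Half-width = t(0.975, 21) × SE = 2.08 × 1.41 = 2.94.
- The whole CI exceeds 2 once the estimate exceeds 2 + 2.94 = 4.94 points.

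| SD | SE | Half-width | Estimate above which L > 2 | Same, in SD units |
|---|---|---|---|---|
| 3 | 1.06 | 2.21 | 4.21 | 1.40 |
| 4 | 1.41 | 2.94 | 4.94 | 1.24 |
| 5 | 1.77 | 3.68 | 5.68 | 1.14 |

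These thresholds sit well inside a 0–20 scale, but they are large effects. Widening ρ to 0–0.7 gives half-widths of 1.82 to 4.24 and thresholds of 3.82 to 6.24 points.

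**4. How often?** P(L > 2) is the chance that a noncentral t on 21 df, with noncentrality (true benefit - 2)/SE, exceeds 2.08. Simulation agrees.

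| True benefit (points) | SD 3 | SD 4 | SD 5 |
|---|---|---|---|
| 2 (the MCID) | 2.5% | 2.5% | 2.5% |
| 3 | 14% | 10% | 8% |
| 4 | 44% | 27% | 19% |
| 5 | 77% | 53% | 37% |
| 6 | 95% | 77% | 58% |

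With ρ from 0 to 0.7 as well, the 4-point figure runs from 15% (SD 5, ρ = 0) to 59% (SD 3, ρ = 0.7). Better retention makes the clause bite more often: with 15 per arm, SD 4 and ρ = 0.5, it is 33% at 4 points instead of 27%.

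**5. Literal rule against an upper-limit rule** (E > 0 and U ≥ 2), at SD 4, ρ = 0.5, n = 12:

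| True benefit | P(go), literal | P(go), upper limit at least 2 |
|---|---|---|
| 0 | 0.50 | 0.50 |
| 2 | 0.90 | 0.92 |
| 4 | 0.73 | 0.998 |
| 6 | 0.23 | 1.00 |

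The literal rule turns down beyond the MCID; the upper-limit rule does not. At zero true effect the two rules differ by 0.001 or less.

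**The case against.** The strongest defence is that the text says *if*, not *only if*. It gives conditions under which the team will go ahead, and it does not say that an interval wholly above 2 stops the programme. A reader might infer that the protocol orders the definitive trial to be abandoned after too good a result. The documents do not support that: the case is not addressed, and no sensible team would decide so. What stands is narrower. A progression criterion is naturally read as the test to be passed, and this one, stated twice, is not passed by the best results.

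The second defence concerns size. At the MCID the clause bites in 2.5% of trials, and it becomes frequent only at about twice the MCID or more. Background itself warns that high-quality CBTp trials give smaller effects. The analysis is described as mostly descriptive, and the estimate and interval would be reported whatever the rule said. All of this stands, and it limits the severity.

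A reader might also infer that the rule mixes scales, because Background states it on the effect size and Planned analysis reports effect sizes as Cohen's *d*. That is not a separate error. Planned analysis also uses the term effect size for the unstandardised difference, places the interval directly after the ANCOVA differences, and gives the MCID in points.

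Finally, an interval wholly above the MCID might be said to make a definitive trial unnecessary. The protocol never says so, and its Discussion holds routine use to be inadvisable while effectiveness is unknown.

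**Conclusion.** The point holds in a limited form. As worded in both places, the rule is not met by a 95% CI lying wholly above 2 points, and nothing else in the protocol covers that case. This follows from the wording alone.

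The frequencies rest on assumed values (SD 3 to 5, correlation 0.5, 12 per arm). On those, the practical effect is negligible at the MCID, modest at 3 points and substantial only from about 4 points upward. Severity is moderate: this is the pilot's stated decision rule and it is mis-specified at its favourable end, but the intent is clear, and no estimate, interval or participant's care is affected.

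**What to change.** In the aims paragraph of Background and in Planned analysis, replace the containment condition with: *the upper limit (in favour of CBTv) of the 95% CI for the baseline-adjusted difference in HPSVQ voice impact points is at least 2*. Keep the first condition, that the estimate favours CBTv.

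This says that the MCID has not been ruled out, makes the rule monotone in the observed benefit for a given interval width, and names the raw-point scale in both places. The cost is one clause in two places, with no change to data collection, sample size or participants, and no easier passage for an ineffective therapy.
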